## Abstract

**Aim:**

This study aims to investigate the concerns of Iranian pregnant women in the antenatal anomaly screening process (AASP) and propose an intervention to reduce these concerns.

**Design:**

This exploratory sequential mixed‐methods study is conducted in three stages (qualitative, intervention design and quantitative), in Tehran.

**Methods:**

A qualitative study is carried out to collect pregnant women's concerns during the AASP. Then, a two‐step procedure is implemented. In the first step (expert session), the concerns extracted in the qualitative part are prioritized. Next, the interventions used to reduce the concerns of pregnant women in the AASP are reviewed by considering the priority determined in the previous stage. The information obtained from this step is used to design intervention. Ultimately, a randomized controlled trial is used to evaluate the effectiveness of the intervention.

**Discussion:**

The results can be used for framing policies in health systems to address pregnant women's concerns in the AASP and to promote their mental health.

AbbreviationsAASPantenatal anomaly screening processAASTsantenatal anomaly screening testsDASSDepression, Anxiety and Stress ScaleNGTnominal group techniqueSPSSStatistical Package for the Social SciencesWKweeks

## INTRODUCTION

1

Chromosomal disorders with a prevalence of 4 in 1,000 live births are among the important determinants of paediatric health and a healthy population. Trisomies constitute almost half of all chromosomal abnormalities (Wellesley et al., 2012). Down syndrome is the most common non‐lethal trisomy and occurs one per 740 live births in the United States (Parker et al., 2010), indicating an increase of approximately 33% compared with the late 1970s (Shin et al., 2009). This increase in prevalence is associated with increased maternal age in this period. According to the guidelines of the American College of Obstetrics and Gynecology, all pregnant women should be offered aneuploidy screening or diagnostic testing in early pregnancy (ACOG & May, 2016).

According to the current birth rate in Iran, about 3,000 cases of Down syndrome are expected annually among all live births. As a result of growth in late marriage and pregnancy and increased maternal demand for foetal health screening, the relevant technological facilities available in Iran's health system should be used for Down syndrome screening. According to the Iranian National Guideline for prevention of foetal chromosomal abnormalities, Down syndrome and trisomy 18 and 13, screening tests are recommended to all pregnant women, and the purpose of the screening should be explained to them from Day 1. The current policy for antenatal anomaly screening tests (AASTs) in Iran, depending on the time of attending perinatal care centres, includes ‘the first trimester combined test’ (nuchal translucency, pregnancy‐associated plasma protein‐A and human chorionic gonadotropin, between 11 weeks (WK) and 13 WK and 6 days of gestation) or ‘quadruple tests’ (human chorionic gonadotropin, alpha‐fetoprotein, unconjugated estriol and inhibin‐A, between 14WK and 16 WK and 6 days of gestation) (Ministry of Health and Medical Education, 2017). In Iran, performing AASTs is voluntary but, due to the high costs of caring for children with Down syndrome, most people choose to have these tests performed despite their high costs. However, most pregnant women are covered by government insurance that pays most of the nuchal translucency and other foetal examination ultrasounds costs.

Regardless of the stress and anxiety associated with pregnancy‐related tests and ultrasound examinations, pregnancy alone can cause stress and anxiety in many women (Georgsson Öhman et al., 2004). Pregnant women might experience varying degrees of anxiety during pregnancy. In this regard, many women experience emotional distress during the first and third trimesters (Georgsson Öhman, 2005). It is very important to address maternal concerns during pregnancy because the mental state of pregnant mothers has a relationship with the occurrence of low birth weight and cesarean delivery (Bastani et al., 2006; van Bussel et al., 2009; Matthey et al., 2003; Robertson et al., 2004). These anxieties and worries affect the mothers' sleep quality, as well as the quality of life, and can have such psychological consequences as postpartum depression (Jomeen, 2004).

## BACKGROUND

2

Little is known about the adverse effects of AASP on pregnant women and their families. Few studies have used qualitative approaches to explore mothers' concerns about AASTs. The majority of studies on women's concerns about AASTs have been conducted in developed countries (Allison et al., 2011; Kaasen et al., 2010; Leiva Portocarrero et al., 2017; Lou et al., 2016), whereas these concerns are expected to be different in developing countries.

Qualitative studies have showed women's concerns in the process of undergoing AASTs from different angles (Carroll et al., 2000; Chiang et al., 2006; Gitsels‐van der Wal et al., 2015; Gottfreðsdóttir, 2009; Lewis et al., 2016; Potter et al., 2008; Reid et al., 2009; Tischler et al., 2011; Williams et al., 2005). For instance, a systematic review, conducted by Reid et al., examined factors affecting pregnant women's decisions regarding accepting or rejecting AASTs. They identified five important themes (destination unknown; to choose or not to choose; the risk is rarely pure and never simple; treading on dreams and betwixt and between) (Reid et al., 2009). In another qualitative study, carried out by Lou et al. in Denmark, the experiences of women and their spouses were investigated while waiting for the results of diagnostic tests, as well as the strategies they adopted to cope with anxiety and distress. Based on the results of this study, all couples experienced anxiety and fear while waiting for the results of diagnostic tests and used strategies, such as isolation or social engagement, to deal with anxiety. However, no measure was taken to manage the waiting time in these cases (Lou et al., 2016). Other studies have explained the views, perceptions and experiences of general practitioners and midwives regarding counseling for AASTs (Dodampahala & Wijeratne, 2014; Gitsels–van der Wal et al., 2014; Martin et al., 2014; Nagle et al., 2008). For instance, Dodampahala qualitatively investigated how physicians and midwives provided counselling to obtain the consent of pregnant women for screening tests and concluded that the counselling process was insufficient and inadequate time was devoted to this issue (Dodampahala & Wijeratne, 2014).

As diagnostic results are normal in the majority of the women with high‐risk AASTs, these unreasonable concerns are the main psychological and social costs these women pay for screening tests. Promoting professional support during these stages might manage these concerns and their associated distress (Peñacoba‐Puente et al., 2011). In Iran, most of the studies on pregnancy concerns have a quantitative design (Kordi et al., 2015; Yousefi, 2015). Quantitative research in understanding the context in which people live is weak (Creswell & Plano Clark, 2018). Maternal concerns during pregnancy have cultural, social, economic and medical dimensions. Therefore, the first step in understanding this concept is to conduct qualitative studies. Furthermore, knowledge of maternal concerns during pregnancy makes it possible to adopt proper strategies to improve their health, quality of life and pregnancy experiences (Peñacoba‐Puente et al., 2011; Puente et al., 2011). There is not any proper qualitative study on the concerns of pregnant women during the AASP, especially on the existing socio‐cultural context of Iran.

The mixed‐methods studies are often based on the pragmatism philosophical approach. Instead of methodology, pragmatic mixed methods are concentrated on the primary research question(s). Although Peirce, Dewey and James are all known as pragmatists, their pragmatism fits more to quantitatively driven mixed methods, convergent or equal‐status mixed methods, and qualitatively driven mixed methods, respectively. In James' pragmatism, the focus is on the practical concepts and outcomes of certain approaches used to describe a phenomenon. Pluralistic ontological and epistemological studies are also emphasized in James' pragmatism (Younas et al., 2019). This study is based on James' philosophy of pragmatism. Based on this approach, the mixed use of qualitative and quantitative methods leads to a better insight into the studied phenomenon and provides much evidence for studying a research problem than either quantitative or qualitative research alone (Creswell and Plano Clark, 2018). According to this fact that there is little information and no specific interventions in the field of pregnant women's concerns about AASTs, the researcher intends to conduct a multiphase exploratory sequential study for explaining the pregnant women's concerns in the process of undergoing AASTs and to design and evaluate interventions in this regard.

## PURPOSE OF THE STUDY

3

This exploratory sequential mixed‐methods study will be implemented in three stages (qualitative stage, intervention design stage and quantitative stage). The objectives of each stage are as follows:

### Objective of the first stage: qualitative study

3.1

Explaining the pregnant women's concerns in the process of antenatal anomaly screening tests.

### Objective of the second stage: intervention design

3.2

Designing an intervention program based on data extracted from the qualitative stage and literature review.

### Objective of the third stage: quantitative study

3.3

Investigating the effect of designing intervention programs on reducing pregnant women's concerns in the process of antenatal anomaly screening tests.

## METHODS

4

### Study design

4.1

This is an exploratory sequential mixed‐methods study. An exploratory sequential design is a biphasic mixed study in which the researcher qualitatively explores the intended subject before building the quantitative study (Creswell and Plano Clark, 2018). In the first part of this study, a qualitative study with a content analysis approach will be conducted to explain the pregnant women's concerns associated with the AASP. To identify the concerns of pregnant women, individual, semi‐structured and in‐depth interviews will be conducted with a focus on pregnant women who have received counseling for undergone AASTs. Purposive sampling will continue in health centres and hospitals, affiliated with the Tehran University of Medical Sciences until data saturation is achieved. Afterwards, during the intervention design stage, a two‐step process will be carried out; in the first step, a panel of experts will be held, including the research team and a group of experts in various health fields with experiences in providing services to pregnant women. In this meeting, the concerns extracted in the qualitative part of the study will be prioritized using the Nominal Group Technique (NGT), and the panel's viewpoints will be collected. In the second step (designing the intervention), the interventions, programs and instructions to reduce pregnant women's concerns in the process of AASTs in Iran and other countries will be investigated by considering the main priority identified in the previous phase. The information obtained from this phase will be used to develop and design an intervention to reduce pregnant women's concerns in the AASP. Finally, in the final step (quantitative part of the study – intervention test), a randomized controlled trial will be performed. In the quantitative part of the study, after completing the questionnaires, data analysis will be performed using SPSS and descriptive and inferential tests. Finally, based on quantitative results, the researcher will interpret the extent to which the designed intervention has been able to reduce pregnant women's concerns about AASTs (Figure 1).

**FIGURE. 1 nop21012-fig-0001:**
[figure not shown]
Study visual diagram

### First stage: a qualitative study

4.2

The first stage of this study is designed to answer the question of ‘What are the concerns of pregnant women about antenatal anomaly screening tests?’ This study will be carried out using a qualitative content analysis method.

#### Participants in the qualitative stage

4.2.1

The study population of the first stage will include pregnant women attending health centres and hospitals affiliated with Tehran University of Medical Sciences for prenatal care.

#### Sampling method

4.2.2

In this study, the participants will be selected with a maximum variation in age, parity, the desirability of the pregnancy, job, education and social status, using purposive sampling.

#### Inclusion criteria for participants

4.2.3

Pregnant women attending perinatal care centresIranian nationality and the ability to speak and understand FarsiWillingness to participate in the study and sharing relevant experiences

#### Research environment

4.2.4

The participants are accessed through health centres and university hospitals affiliated with Tehran University of Medical Sciences, midwifery departments and perinatology departments. The interviews will be conducted at the participants' preferred time and place to ensure their comfort.

#### Data collection process

4.2.5

Data will be collected after obtaining the approval of the Research Ethics Committee and receiving a letter of introduction from the Tehran University of Medical Sciences. In the first stage, in‐depth personal interviews will be used to collect data. These interviews will be based on an interview guideline. Before the interviews, informed consent will be obtained from the participants. Interviews will be conducted in a location comfortable for participants and will start with communication to win their trust. The participants will be then asked to express their views on their concerns about the AASTs. Subsequent questions will be asked based on the participants' initial answers and the interview guide. Besides, questions, such as ‘what do you mean or explain more please’, will be asked if needed. At the end of the interview, the researcher will ask the participants to state any other opinions and then will talk to them about the possibility of further interviews. The number of interview sessions depends on the participants and their answers to the research questions. The interviews will be recorded and transcribed verbatim with the participants' permission and will be presented to them to check their accuracy. As the interviews continue, the interview guide may be modified, and new questions will be added if necessary.

#### Data analysis

4.2.6

The conventional content analysis approach will be used to analyse qualitative data. In this study, qualitative content analysis will be performed according to Graneheim and Lundman's method (Graneheim & Lundman, 2004). In this method, after each interview, the content will be transcribed at the earliest convenience. The statements will be read word by word several times to gain a general understanding of them. The semantic units will then be identified from the content of each interview. The semantic units – groups of words or phrases that have the same content – will be coded. Then, primary codes that centre around a central concept will be placed in a similar subcategory. Afterwards, the subcategories will be reviewed several times and checked for similarities and differences. Consequently, categories and themes will be formed. Attempts will be made to have the highest homogeneity in the categories and find the most heterogeneity between the categories. A computer‐assisted program MAXQDA 10 will be used to manage the data (Kuckartz, 2010).

#### Determining the validity and reliability of data

4.2.7

Five criteria are suggested for reliability and validity analysis: credibility, dependability, transferability, confirmability and authenticity (Polit & Beck, 2008). Several methods will be used to confirm the validity: member check; external check; peer debriefing; prolonged engagement with the data; data triangulation, such as using interviews and field notes; and maximum variation sampling in terms of age, education, career, living place and stage of tests In this research, external check and peer debriefing will be used to confirm dependability, and samples of scripts and codes will be sent to the participants to monitor the data analysis process and apply their positive and critical opinions.

Due to the nature of qualitative research that lacks transferability, the researcher will try to accurately record the research path and the decisions made in this process and write her dissertation on the subject to enable other investigators to have a correct estimate of the generalizability of the findings. To this end, the researcher will accurately describe the participants, sampling method and time and place of data collection and will perform sampling with maximum variation in terms of age, living area, level of education, occupation and different social classes to enable the reader to use these findings in other contexts and situations to enhance the generalizability of the findings.

To ensure confirmability, interview transcripts, and extracted codes and categories will be provided to the research team and a faculty member to verify the accuracy of the process. Furthermore, different phases of the study will be presented very clearly to enable other participants to follow and judge the appropriateness of the research process To establish sincerity, the researcher will try to relate the participants' statements, feelings and experiences honestly. In addition, the audio files, interview transcripts and extracted codes and categories will be provided to the research team members to check the authenticity of the process and the reports.

### Second stage: Intervention designing

4.3

Results from the data collection process in the qualitative stage will inform the data collection approach of the second stage procedure. In fact, the information obtained from the qualitative study will show us the search path in the studies and the selection of the intervention type based on the experts' opinions. Then the suitable intervention program will be selected and implemented in the quantitative phase based on this prioritization. In the second stage of the study, two steps will be completed for designing and implementing interventions to reduce the concerns of pregnant women.

#### Prioritizing concerns

4.3.1

At this stage, the pregnant women's concerns, extracted in the qualitative part of the study, will be prioritized by investigating the views and opinions of the expert panel who have experience in providing health care or medical services to pregnant women. During this stage, an expert meeting will be organized using the NGT. This method supports the equivalent participation of group members as it limits the power of individual decision‐making and allows all members of the group to express their opinions equally by balancing each individual's influence (Wortley et al., 2016). This technique will be implemented in four stages, including generating ideas, reporting and recording ideas, discussing ideas and ultimately voting to rank ideas (Control and C. F. D. & Prevention., 2006). For voting, group members will be requested to select five of the most important recorded concerns (themes and categories), privately and anonymously, without consulting others and rank them according to their importance and feasibility of intervention design from 1 (least important) to 5 (most important). Finally, the researcher will count and combine the votes in the presence of all participants. Accordingly, a concern obtaining the highest score will be considered the most desired and important concern for which intervention will be designed.

#### Designing the intervention

4.3.2

At this stage, the interventions and programs for promoting pregnant women's physical and mental health in Iran and other countries will be investigated considering the main priority set in the previous stage. Accordingly, Google Scholar, PubMed, ScienceDirect, Cochrane Library, Scopus, Magiran and SID will be searched, and different combinations of keywords will be reviewed between 2000 and 2020. Then, the related interventions and programs will be evaluated. Therefore, using the results of the qualitative study and reviewing the literature, a list of recommendations will be developed and prioritized. According to the information obtained from this stage, the target group, purposes and primary content of the intervention will be designed with the guidance of supervisors and advisors.

### Joint displays

4.4

A joint display is a table that appears as a structure to discuss the integrated analysis and help both researchers and readers in understanding how a mixed‐methods provides new insights (Guetterman et al., 2015). We will have two joint displays in this study. A decision‐making matrix (first joint display) will be used for the prioritization of the extracted data from the qualitative study. This matrix consists of columns of ‘the themes and categories’, ‘scoring with respect to importance and the possibility to design interventions for themes and categories by the experts’, ‘the information obtained from the search process’ and ‘the type of the designed intervention’. We will use the second joint display to present a graphical and content analysis of the inferences from the qualitative and quantitative phases, and the comprehensive conclusions will determine by merging the individual inferences (Creswell and Plano Clark, 2018).

### Third stage: A quantitative study

4.5

The quantitative stage of the study will be carried out using a randomized controlled trial.

#### Research population

4.5.1

The research population of the quantitative study section includes all pregnant women presenting to the prenatal clinics of hospitals and health centres affiliated with Tehran University of Medical Sciences.

#### Research sample

4.5.2

In this section, participants include pregnant women that meet the inclusion criteria and are presented to the prenatal clinics of hospitals and health centres affiliated with Tehran University of Medical Sciences.

#### Research environment

4.5.3

This study will be carried out in health centres and prenatal clinics of hospitals affiliated with Tehran University of Medical Sciences.

#### Sample size

4.5.4

The sample size will be 75 in each group with a confidence interval of 95%, trial power of 80%, Cohen's d of 0.5 and a sample loss of 15%.

#### Sampling method

4.5.5

In the quantitative part of the study, convenience and continuous sampling will be implemented, in that all eligible individuals will enter the study after receiving a detailed explanation about the purpose of the study and signing an informed consent form. Afterwards, the samples will be divided into intervention and comparison groups using permuted block randomization based on Random Allocation Software considering all possible ways of assigning groups to blocks. The size of the blocks will be randomly selected (e.g., blocks containing 4, 8, 12 and 16 persons equally divided in each group). By selecting blocks randomly, the possibility of disclosing the last allocation in each block will be eliminated (Elkins, 2013; Kang et al., 2008).

This study will be an open‐label trial as masking of intervention is not possible. One of the researchers' colleagues will make the allocation sequence, and the researcher will register the participants and assign them to the intervention and control groups. All participating women will complete the initial questionnaires after randomization. The intervention group will be contacted and informed about the implementation of the intervention.

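### One unmasked researcher both enrols and assigns women, baseline follows randomisation, and random block sizes are said to eliminate a predictability that they only reduce

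*Protocol article*

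**What the plan says.** Section 4.5.5 (Sampling method) fixes the following:

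- **Masking:** "This study will be an open‐label trial as masking of intervention is not possible".
- **Sequence:** "One of the researchers' colleagues will make the allocation sequence", "using permuted block randomization based on Random Allocation Software". Block sizes are drawn at random, with 4, 8, 12 and 16 offered as examples, and each block is split equally between the arms.
- **Enrolment and assignment:** "the researcher will register the participants and assign them to the intervention and control groups".
- **Protection claimed:** "By selecting blocks randomly, the possibility of disclosing the last allocation in each block will be eliminated".
- **Order of events:** "all eligible individuals will enter the study after receiving a detailed explanation about the purpose of the study and signing an informed consent form". Allocation comes next, and the initial questionnaires are completed after randomisation.

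Section 4.5.10 repeats the order of consent and then permuted blocks, and adds nothing on how an arm is released. Section 4.5.6 requires a significant level of worry about screening but gives no cut-off. Section 4.5.7 says that the criteria will be revised after the qualitative stage.

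**The concern.** Three stated rules combine badly. The person who enrols also assigns. She is unmasked, so she learns each arm as she goes. The only protection against prediction that the article offers is the random block size, and the article overstates what that achieves.

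Foreknowledge, even if only probabilistic, can be acted on before consent. The explanation given to a woman can be more or less encouraging, and the worry criterion, as it now stands, is a matter of judgement. Because the initial questionnaires come after randomisation, the text also provides no logged baseline score that predates the arm.

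Selection of this kind would shift the between-arm comparison in a way that the planned t test (Section 4.5.11) cannot detect. Adjustment for measured covariates would not recover selection on unmeasured ones.

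**Working it through.** **1. The plan's own figure.** Section 4.5.4 gives 75 per group from d = 0.5, 80% power, 95% confidence (read as two-sided alpha 0.05) and 15% loss. The normal-approximation formula is n = 2(1.960 + 0.842)² / 0.5² = 62.8, so 63. Then 63 / 0.85 = 74.1, so 75. The figure reproduces, and the total is 150 allocations.

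**2. Predictability.** Assumptions: sizes 4, 8, 12 and 16 equally likely, one recruiter, all past arms visible. The rule is to guess the arm with fewer women so far, and to guess at random when the arms are level. The arms are level at the end of every complete block, so the rule needs no knowledge of block sizes or boundaries.

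For a complete block of 2m, the expected number of correct guesses above m is 4^m / (2·C(2m, m)) − 1/2.

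| Block size | Excess correct guesses | Share correct |
|---|---|---|
| 4 | 16/12 − 0.5 = 0.833 | 70.8% |
| 8 | 256/140 − 0.5 = 1.329 | 66.6% |
| 12 | 4096/1848 − 0.5 = 1.716 | 64.3% |
| 16 | 65536/25740 − 0.5 = 2.046 | 62.8% |

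Weighted by block length, the share is 0.5 + (0.833 + 1.329 + 1.716 + 2.046)/40 = 0.5 + 5.924/40 = 64.8%. A simulation of 2,000 sequences of 150, in which the final block may be cut short, gave 64.6%, or about 97 of 150 against 75 by chance.

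**3. The narrower claim about the last allocation.** Just before the last place in any complete block, one arm is exactly one behind, and that arm comes next. The rule is therefore right at the last place of every complete block, whatever its size. What random sizes remove is mostly the recruiter's *certainty* that she has reached that place, and they do not remove all of it. In the simulation, a recruiter who knew the set of sizes but not the boundaries could still predict about 1.9 of 150 allocations with certainty, and about 59% of simulated trials contained at least one. About 32 of 150 were predictable with probability 0.75 or more. With fixed blocks of 4, about 33% of allocations are certain, so the random sizes do help.

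**4. Size of the bias.** Suppose that women steered towards the two arms differ in prognosis by δ, and that a fraction p of guesses is right. The arm means shift by +(2p − 1)δ/2 and −(2p − 1)δ/2, so the spurious difference is δ(2p − 1). With p = 0.648, 2p − 1 = 0.296.

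| Assumed δ (SD) | Spurious difference (SD) | Share of d = 0.5 |
|---|---|---|
| 0.1 | 0.030 | 6% |
| 0.3 | 0.089 | 18% |
| 0.5 | 0.148 | 30% |

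For each δ this is an upper limit. It assumes that every slot is steered and that a suitable woman is always at hand.

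**The case against.** **The stronger reading.** A reader might infer that the researcher works from the list and so knows every arm in advance. Prediction would then be 100% and the bias the full δ, for example 0.30 SD at δ = 0.3. The article does not support this. It gives sequence generation to a colleague and does not say who holds the sequence or how an arm is released. Assigning could mean opening an envelope or phoning the colleague. Those figures hold only if the recruiter can see the list.

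**A condensed article may omit the release device.** This is fair, and a missing mention of envelopes or a telephone service is not the point here. The division of roles, the timing of baseline and the word eliminated are all stated. A fuller document could add a release step, but it could not make the claim true.

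**The claim covers only the last allocation of each block.** This is correct; the article does not say that random sizes conceal the whole sequence. The narrower claim still fails (step 3), although the design choice clearly works in the right direction.

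**Envelopes or phone release would leave the 65% unchanged.** This stands. The guess uses only past arms, which an unmasked recruiter sees in any case. A fix has to limit what she learns about past arms as well as guard the list.

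**Steering may be limited.** This also stands in part. All eligible women are meant to enter, consent precedes allocation, several centres take part and the worry criterion is provisional. These points lower the bias below the limits in step 4. They do not bring it to zero, because prediction acts before consent.

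**Conclusion.** The point holds in a bounded form. The article states that one unmasked researcher enrols and assigns, that baseline follows randomisation, and that random block sizes eliminate disclosure of each block's last allocation. That last statement is wrong: predictability is reduced, to about 65% correct guesses against 50%, and is not eliminated.

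The 65% rests on the example block sizes being used with equal probability and on one recruiter seeing all past arms. The possible bias is at most about 0.03 to 0.15 SD for an assumed δ of 0.1 to 0.5 SD, and it scales with that assumption. The document gives no value for δ. Complete loss of concealment is a risk that the text leaves open, not something that it describes.

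**What to change.** Amend Section 4.5.5, and Section 4.5.10 to match, before the first woman is randomised:

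1. The colleague who makes the sequence keeps it and makes each assignment, one woman at a time. The recruiting researcher has no access to it.
2. An arm is released only after consent, confirmed eligibility and the completed baseline questionnaire are irrevocably logged. This moves baseline before randomisation.
3. Block sizes are withheld from the recruiter. This removes the certain predictions that depend on knowing the sizes, but not the guess based on which arm is behind.
4. Where feasible, the colleague and not the recruiter tells each woman her arm, so that past arms are less available for prediction. If the recruiter never learned past arms, the guess rate would return to 50%. If she must learn them, for instance because she delivers the intervention or makes the follow-up calls, some predictability remains and the protocol should say so.
5. Say that disclosure of the last allocation will be reduced, not eliminated.

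The sample size stays at 75 per group. The colleague is already in the plan, so the cost is minor logistics for that person across 150 assignments.
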